### Randomization

Patients will be allocated randomly using a Web-based computer program http://www.randomizer.at. Balance of treatment counts is achieved by the biased-coin method with probability 0.7 [40]. Randomization will occur shortly after receipt of the second urinary NGAL value. NGAL determinations will be made by the medical technical staff of the Clinical Institute for Laboratory Medicine, Medical University of Graz, Austria. The criteria for randomization (after 2^nd ^NGAL testing, 4 -6 hours following CM application) are:

• Patients with NGAL levels > 150 ng/ml, if baseline was below 75 ng/ml [23].

• Patients with doubling of NGAL values, if baseline values were > 75 ng/ml [18].

### Procedure following randomization

Study patients with a defined increase of urinary NGAL values at 4 to 6 hours after CM application will be randomized into one of two groups:

Patients of **Group A **will receive 3-4 ml/kg BW/h 0.9% saline intravenously for 6 hours post procedure in addition to oral fluid.

Patients of **Group B **will receive unrestricted oral fluid. An intake of at least 500 ml tea or water is advised and provided on the ward.

### Blinding

Blinding of investigators and patients is not feasible as it is immediately recognizable and impossible to conceal that only one group (Group A) receives saline intravenously.

### Outcome measures

#### Primary outcome measure

CIN defined by an increase greater than 25% of baseline serum creatinine. Additionally, patients will be classified according to the Cockcroft and Gault, as well as the MDRD and the CKD-EPI calculation formula.

#### Secondary outcome measures

Urinary NGAL values, cystatin C values, contrast media associated changes of cardiac parameters such as NT-pro-BNP/Troponin T, changes in urinary cytology, need for renal replacement treatment, length of hospital stay and death.

#### Monitoring for adverse events

The study investigators and the Coordination Center for Clinical Studies, Medical University of Graz, authored a standardized operating procedure for reporting adverse events. Although this trial has not been declared as a pharmacological interventional study, because the volume expansion is considered a physical rather than a pharmacological effect, the investigators voluntarily chose to report adverse events according to the guidelines for a pharmacological interventional study. All relevant adverse events will be summarized and reported to the Ethics Committee of the Medical University of Graz.

### Data collection

Historical data will be obtained from the patient or collected from medical records. These include age, gender, weight, height, relevant co-morbidities, existence of peripheral edema, current medication, contrast media dose and location of angiography/angioplasty/stent implantation. Furthermore, there will be repeated lab studies including complete blood count, electrolytes, serum creatinine, coagulation profile, liver function test, C-reactive protein, bicarbonate and spot urine analysis and urinary NGAL. Length of hospitalization will documented. All data are stored in an electronic case report form.

### Sample size calculations

Sample Size: Alpha = 0.05, power = 0.8, two-sided test. Assuming a clinically relevant difference in CIN incidence of 20% and 60% CIN in the control group (worst case), 108 patients per group are required for the chi square test. Only patients who meet the NGAL criteria for randomization will be included. We assume that 20% of the included patients, which would amount to about 1200 patients, will be randomized to treatment groups. If fewer than 48 patients are randomized after the inclusion of 240 patients, the NGAL criteria for randomization will be adapted in order to meet the objective of including not more than 1200 patients. Recruitment will continue until 240 patients have been randomized.

Analysis: Chi square tests will be used for CIN reduction. Wilcoxon's rank sum test will be applied to continuous measurements.

### Statistical considerations

The diagnostic value of a two-point-measurement of NGAL, cystatin C and creatinine before and after CM application, as compared to a single-point-measurement only after CM application with respect to CIN will be assessed through receiver operating characteristic (ROC) within the patients who received standard therapy. The analysis has to account for the bias that is caused by the exclusion of patients who receive treatment A from ROC analysis on the condition of an elevated NGAL. The available sample size for ROC analysis is determined by the number of patients, the incidence of CIN and the number of patients who receive treatment A. We assume that 20% of the included patients will develop CIN.

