### Aims of our study

1). To evaluate the true risk of CIN in high-risk patients following intra-arterial angiography using a standardized pre-procedural protocol for intravenous volume load.

2). To evaluate the benefit of an earlier diagnosis of renal damage after investigation using urinary NGAL.

3). To investigate the effect of a well-timed and intensified post-procedural volume expansion on renal function, morbidity and mortality in patients predicted to develop CIN according to NGAL testing.

4). To study NGAL in patients with mild, moderate and severe CKD (stage 2-4), a subgroup of individuals who frequently develop CIN. At present it is still unclear whether the new biomarker NGAL is comparably effective in this particular group.

5). To define and establish a reliable cut-off value or pattern of increase for NGAL in patients with chronic renal failure and to estimate its sensitivity and specificity.

6). To assess the value of a 25% increase in serum creatinine as a definition for clinically relevant CIN.

7). To compare the value of NGAL and cystatin C in predicting CIN.

8). To compare the value of the MDRD, the CKD-EPI- and the Cockcroft-Gault formula in this particular patient group.

At this stage, little is known about the beneficial effect of earlier diagnosis and subsequent intervention by volume expansion on AKI due to a rise in urinary NGAL. As the time course of kidney damage is usually not apparent, contrast media induced nephropathy (CIN) is a promising condition for this question. Results from previous studies are unable to guide the clinician when baseline urinary NGAL levels exceed the normal range.

To our knowledge, this is the first clinical study to address this problem. We are trying to assess the effect of an early intervention by volume expansion in patients with increasing urinary NGAL levels 4-6 hours following CM application. If a significant reduction of CIN as defined by creatinine levels is found in the treatment arm within 2 days, a clear benefit of measuring urinary NGAL might be postulated. We are currently recruiting patients for this non-commercial investigator initiated trial to elucidate CIN.

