### Standardized procedure

Hospitalized patients scheduled for elective intra-arterial angiography will be prepared for CM application using a weight-based hydration protocol.

Monomeric Iomeron^® ^(iomeprol, Bracco Austria, Vienna) will be used exclusively as contrast media. Blood samples for standard evaluation, including serum creatinine and cystatin C, will be drawn at baseline and after 24 and 48 hours from all patients. A BW/h saline infusion (3-5 ml/kg) will be given for 3 hours before CM application. Urine samples for NGAL testing will be collected shortly before (baseline) and after 4 to 6 hours following CM application. NGAL will be measured with the commercially available ARCHITECT^® ^NGAL Test, Abbott Laboratories, Abbott Park, Illinois, U.S.A. [15,39].

Patients who develop CIN will be treated and followed at the Division of Nephrology and Hemodialysis according to established standards.

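### Two-point creatinine is tested by ROC against CIN, which is itself a creatinine rise over the same draws; separately, the NGAL versus cystatin C aim sets markers from different times side by side

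*Protocol article*

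**What the plan says.** All places are in the Protocol article.

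- **Index tests** (Statistical considerations): "The diagnostic value of a two-point-measurement of NGAL, cystatin C and creatinine before and after CM application". This is set against a measurement taken only after contrast: "as compared to a single-point-measurement only after CM application with respect to CIN will be assessed through receiver operating characteristic (ROC").
- **Outcome** (Primary outcome measure): "CIN defined by an increase greater than 25% of baseline serum creatinine". That section gives no time window. Aims of our study supplies one: "If a significant reduction of CIN as defined by creatinine levels is found in the treatment arm within 2 days".
- **Creatinine and cystatin C sampling** (Standardized procedure): "Blood samples for standard evaluation, including serum creatinine and cystatin C, will be drawn at baseline and after 24 and 48 hours from all patients".
- **NGAL sampling** (same section): "Urine samples for NGAL testing will be collected shortly before (baseline) and after 4 to 6 hours following CM application".
- **Comparison of markers** (Aims of our study, aim 7): "To compare the value of NGAL and cystatin C in predicting CIN".

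Statistical considerations acknowledges one bias, from leaving patients given treatment A out of the ROC analysis. It does not mention the overlap between creatinine and the outcome, or the different sampling times. It does not say which post-contrast draw enters the ROC.

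**The concern.** There are two separate problems.

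**Creatinine.** An index test should carry information that is not already part of the reference standard. Here the post-contrast creatinine value is one of the values that decide whether the patient has CIN, and the baseline value is the denominator of that decision. A high AUC for the two-point change would restate the definition of CIN. It would also settle in advance, for creatinine, the question the ROC analysis asks: whether two points beat one.

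**NGAL and cystatin C.** NGAL is read at 4–6 h; cystatin C comes from the blood draws at which CIN is declared. If aim 7 were answered by comparing AUCs, a marker read at or near diagnosis would be set against one read most of a day or more before it. The Background's case for NGAL is the time it gains, and an AUC gives no credit for that.

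**Working it through.** **Figures in the plan.** The ROC analysis has no stated AUC, precision target or sample size, so there is no figure of its own to reproduce. The one computed sample size, 108 per group for the treatment comparison (60% versus 40% CIN, two-sided alpha 0.05, power 0.8), comes out at 107 with a continuity correction. It does not depend on the ROC analysis.

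**Step 1: overlap of draws.** Write R24 and R48 for the ratios of 24 h and 48 h creatinine to baseline.

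- CIN by 48 h: R24 > 1.25 or R48 > 1.25.
- Two-point creatinine index: R24 or R48.

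On the stated schedule, every available index value is also an input to the outcome.

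**Step 2: same draw.** If the index is the ratio that defines CIN, every case lies above 1.25 and every non-case at or below it. The AUC is 1.0 by construction.

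**Step 3: 24 h change as index.** Taken from the document: 20% CIN (Statistical considerations). Assumed, because the document gives neither: log R24 and log R48 bivariate normal with equal variances, and their correlation. The threshold is placed so that 20% have CIN. The AUC depends only on ranks, so with prevalence fixed the SD drops out. Simulation with 1,000,000 draws per row:

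| Assumed correlation | AUC, CIN at 24 or 48 h | Share of CIN already present at 24 h | AUC, CIN judged at 48 h alone |
|---|---|---|---|
| 0.6 | 0.914 | 63% | 0.80 |
| 0.8 | 0.959 | 72% | 0.90 |
| 0.9 | 0.981 | 79% | 0.95 |

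In the second column the specificity at the 25% cut is 100% by definition, since anyone above the cut at 24 h already has CIN. The last column is the one reading without overlap, and the document does not state it.

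**Step 4: how much comes from the overlap.** Among simulated patients without CIN at 24 h, the AUC of the 24 h change for CIN first appearing at 48 h is 0.76, 0.86 and 0.91 at the same three correlations, against 0.91, 0.96 and 0.98 above.

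**Step 5: two points versus one.** With a further assumed log SD of 0.3 for baseline creatinine, zero mean log change and the SD of change set to give 20% CIN, a single 24 h creatinine level has an AUC of 0.71 to 0.79 over correlations 0.5 to 0.9. The two-point 24 h change has 0.89 to 0.98 over the same range. That gap arises because the outcome is itself a two-point change. It says nothing about whether two-point testing helps for another marker.

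**Step 6: timing of NGAL and cystatin C.** The shortest gap is 24 − 6 = 18 h and the longest is 48 − 4 = 44 h. Cystatin C at 24 h coincides with diagnosis for CIN present at 24 h and precedes it for CIN first seen at 48 h. Cystatin C at 48 h never precedes CIN declared by 48 h. The direction of the advantage follows from this. Its size does not, because the document gives no data on how either marker relates to CIN over time.

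**The case against.** The best defence is that the plan does not say what a hurried reader may take from it.

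- **A reader might infer that the whole marker analysis is circular.** It is not. Cystatin C and NGAL are not part of the definition of CIN. Two-point versus single-point NGAL, the contrast the Discussion motivates, has no such overlap.
- **A reader might infer that the ROC section itself ranks cystatin C against NGAL.** It does not. Its stated contrast is two-point versus single-point. The comparison of the two markers appears as aim 7, with no method attached. The timing problem therefore arises only if ROC, the one method described for comparing diagnostic measurements, is used for that aim.
- **A reader might infer that cystatin C cannot predict CIN at all.** That goes too far. Under the assumptions above, 21% to 37% of CIN cases first appear after 24 h, and for those a 24 h value does come first.
- **The draws may not be exhaustive.** Data collection lists repeated creatinine without times, and the study scheme figure is not shown. An article may also leave the choice of ROC time point to a fuller document. This is fair, but no extra draw is documented, and nothing in the text separates the index draw from the outcome draws.
- **The AUCs rest on assumed correlations.** This is correct for the 0.91 to 0.98 range. It does not apply to the 1.0, or to the 100% specificity in Step 3, which follow from the definition.

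The first three points limit the scope of the finding. The last two limit its precision. None removes the overlap for creatinine.

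**Conclusion.** The point holds for creatinine. As written, the plan scores creatinine change against an outcome made from creatinine change. The AUC is 1.0 if the same draw is used, and about 0.91 to 0.98 if the 24 h change is scored against CIN at 24 or 48 h, given 20% CIN and assumed correlations of 0.6 to 0.9. Only a 24 h index with CIN judged at 48 h alone would avoid the overlap, and the document sets no such rule.

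For NGAL and cystatin C the fault is unequal timing. An AUC ranking under aim 7 would tend to favour cystatin C, by an amount that cannot be estimated from the document.

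The finding concerns the secondary diagnostic aims. A reader might infer that it threatens the trial's main result. The documents do not support that: the randomized comparison of CIN, its chi-square test, its sample size, the NGAL criteria for randomization, and the planned sensitivity and specificity of NGAL all stand. It should be corrected, but it is not a condition for the primary analysis to be valid.

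**What to change.** 1. **Statistical considerations:** delete creatinine, both two-point and single-point, as an index test for CIN. Keep NGAL and cystatin C. This is a change of wording and loses no valid information.
2. **Aim 7:** report 4–6 h NGAL for CIN by 48 h as the early-prediction result. Report cystatin C separately by sampling time (24 h, 48 h). State that the two are not ranked by AUC as predictors. This needs no new data. The cost is that aim 7 yields a description by time and no single winner.
3. **Optional secondary analysis:** 24 h cystatin C for CIN first appearing at 48 h, among patients without CIN at 24 h. The price is events: about 21% to 37% of CIN cases under the assumptions above. With 1200 included and 20% CIN that is 240 × 0.21 to 240 × 0.37, or about 50 to 89, before patients given treatment A are removed. It should not replace the NGAL result, because it discards the 63% to 79% of cases already present at 24 h, which early NGAL testing is meant to detect.

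A true head-to-head at one early time would need cystatin C from blood taken at 4–6 h. The Standardized procedure section lists no such draw, so that would be an added procedure and not a change of analysis wording. The correction above does not depend on it.

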### Data analysis

Treatments will be compared according to relative change of creatinine from baseline by the Wilcoxon test and Pearson's chi square test (two-sided, alpha = 0.05).

As mentioned above, those patients without a relevant increase of NGAL will also be followed. This will allow us to retrospectively calculate sensitivity and specificity of NGAL testing for CIN.

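### The primary CIN comparison is fixed as an unadjusted chi-square test, valid but leaving pre-randomisation prognostic data unused, and the Data analysis section does not say that this test, rather than the Wilcoxon test, decides

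*Protocol article*

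**What the plan says.** The analysis of the treatment effect appears in two places in the protocol article.

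- **Sample size calculations.** The design line reads "Alpha = 0.05, power = 0.8, two-sided test", followed by "60% CIN in the control group (worst case), 108 patients per group are required for the chi square test". For the analysis, "Chi square tests will be used for CIN reduction", and the next sentence gives the rank sum test to continuous measurements. The stopping point for recruitment is "Recruitment will continue until 240 patients have been randomized".
- **Data analysis.** Treatments are compared on "relative change of creatinine from baseline by the Wilcoxon test and Pearson's chi square test (two-sided, alpha = 0.05"). Both tests stand under one alpha, with no order and no decision rule.

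Primary outcome measure names one binary endpoint, CIN, as a rise of more than 25% over baseline creatinine. Neither analysis passage mentions a covariate.

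On allocation, Randomization says: "Balance of treatment counts is achieved by the biased-coin method with probability 0.7". No stratification factor is named. Patients are randomised after the second urinary NGAL value, so baseline creatinine, both NGAL values and the contrast exposure all precede allocation. Data collection lists, among other items, "current medication, contrast media dose and location of angiography/angioplasty/stent implantation".

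**The concern.** There are two issues, of unequal weight.

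The main one is efficiency. The article goes beyond silence on the analysis model and fixes an unadjusted test. The trial nevertheless records, before allocation, variables that its own rationale treats as related to CIN. Allocation controls only the number per arm, so chance differences in renal function, NGAL response or contrast dose at about 120 per arm are neither balanced by design nor taken up in the estimate. If those variables predict CIN, precision is lost for no saving.

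The lesser one is clarity. Two tests of the same creatinine change, one continuous and one dichotomised, share one alpha without a stated order. The trial is open label, and one of its aims is to assess whether the 25% cut-off is a good definition of CIN. If the chi-square test missed and the Wilcoxon test did not, the Data analysis section taken alone would not settle which result counts.

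**Working it through.** **Inputs.** Two-sided alpha 0.05, power 0.80, CIN 60% in controls and a 20-point difference (so 60% v 40%), 108 per group, 240 randomised (240/2 = 120 per arm): all from Sample size calculations. CIN of 20% among all included patients: Statistical considerations. Prognostic strength of the covariates: not given, so assumed.

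**1. The plan's own figure.** For two proportions with mean 0.5:

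n = [1.960·√(2·0.5·0.5) + 0.8416·√(0.6·0.4 + 0.4·0.6)]² / 0.2² = (1.3859 + 0.5831)² / 0.04 = 96.9, so 97 per group.

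With continuity correction, n′ = (n/4)·[1 + √(1 + 4/(n·0.2))]² = (97/4)·(1 + 1.0983)² = 106.8, so 107. The stated 108 is reproduced to within one patient.

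Power of the uncorrected test is Φ{[0.2 − 1.960·√(0.5/n)] / √(0.48/n)}: 84.1% at n = 108 and 87.7% at n = 120.

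**2. Type I error under two decision rules.** With no treatment effect, the Wilcoxon statistic on a continuous variable and the chi-square statistic on the same variable cut at event rate p have correlation about √[3p(1 − p)]. A bivariate normal calculation gives the chance that at least one is significant at 5%. A simulation of 40,000 null trials checks it.

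| CIN rate | Correlation | Either test, normal | Simulated, 108/arm | Simulated, 120/arm |
|---|---|---|---|---|
| 20% | 0.693 | 8.4% | 8.2% | 8.3% |
| 40% | 0.849 | 7.5% | 7.3% | 7.4% |
| 50% | 0.866 | 7.3% | 7.1% | 7.0% |
| 60% | 0.849 | 7.5% | 7.5% | 7.6% |

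The range is about 7–8.4%. It lies below the 9.75% for independent tests (1 − 0.95²) because both tests use the same measurements. If the chi-square test on CIN alone decides, the error is 5%.

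If both tests were meant to be confirmatory at 0.025 each, the chi-square test would need 118 per group (128 with continuity correction). Its uncorrected power would be 76.2% at 108 and 80.9% at 120 per group.

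**3. What adjustment could gain (assumption).** Simulation at 60% v 40% and 120 per arm, with one standard normal covariate of log-odds 0.5–1.3, gave explained variance of 5–24% and a variance ratio for the risk difference of 0.96–0.78, a reduction of about 4–22%.

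A hand check at 120 per arm: the unadjusted variance is 0.48/120 = 0.0040, and power ≈ Φ[0.2/√(0.0040·ratio) − 2.00].

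- Ratio 1: Φ(3.162 − 2.000) = 88%.
- Ratio 0.96: Φ(3.228 − 2.000) = 89%.
- Ratio 0.78: Φ(3.581 − 2.000) = 94%.

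The simulation gave 89–95% adjusted against 87–88% unadjusted, so the two agree.

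**4. Events available to the model.** At the planning rates, 0.6·120 + 0.4·120 = 72 + 48 = 120 events. At 20% CIN, 0.2·240 = 48. With arm and three covariates there are four coefficients besides the intercept: 120/4 = 30 events per coefficient in the first case and 48/4 = 12 in the second.

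**The case against.** **On type I error.** A reader might infer that the plan inflates its 5% error. The documents do not support that. Inflation needs a rule that success on either test suffices, and no section states one. There is one primary outcome, binary CIN. The sample size is built on the chi-square test for CIN. The same section gives the Wilcoxon test to continuous measurements. The aims tie the claim of benefit to a significant reduction of CIN. Read together, these make the chi-square test on CIN the deciding test. This objection stands, and it reduces the ordering of the tests to a clarification.

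**On adjustment.** A reader might also infer that the unadjusted test is wrong, or that chance imbalance invalidates it. Neither follows. After randomisation the test is valid, and its 5% error already allows for chance imbalance. Baseline creatinine also enters the outcome as the denominator of the relative change, though not as a covariate. Planned power is met without adjustment.

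The size of the gain is open as well. The article itself says little is known about NGAL in chronic kidney disease. The entry rule also truncates the NGAL ratio: a baseline below 75 with a second value above 150 ng/ml means a ratio above 150/75 = 2, and the other route requires doubling. A strong effect of the ratio within the randomised group cannot be presumed.

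Finally, adjustment is often left to an analysis plan. That would answer a complaint about silence. Here the article names the test in two sections, so the stated choice can be compared with a better one.

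**Conclusion.** The point holds as an improvement to a valid analysis, together with a clarification. The article fixes an unadjusted chi-square test for CIN, and allocation balances arm totals only. Baseline renal function, the NGAL pair and contrast dose are available before allocation at no extra cost.

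The likely benefit is a 4–22% smaller variance of the risk difference, provided that the covariates explain 5–24% of the variance in CIN. That range is an assumption, and the simulation behind it used a single covariate rather than the three proposed. With weaker predictors the gain shrinks towards nothing.

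The error rate is 5% on the natural reading. The 7–8.4% figure applies only under an either-test rule that the article does not state. Its upper end uses the 20% CIN rate given for all included patients; the only rate stated for the randomised patients is 60% in controls. The calculation assumes equal arms and a continuous measurement without ties. The trial should not be described as having an inflated error rate, an invalid test or too few patients on this account.

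**What to change.** In Data analysis:

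1. Name CIN, as defined under Primary outcome measure, as the single confirmatory comparison at two-sided 0.05.
2. Analyse it with a prespecified logistic model containing arm, baseline eGFR (one formula named in advance, since the article lists three), the log ratio of the two NGAL values, and contrast dose.
3. Report a standardised risk difference with 95% CI. This keeps the result on the absolute scale on which the sample size was set.
4. Keep the unadjusted chi-square test and the Wilcoxon test on relative creatinine change, both labelled supportive.

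Because the trial is open label, the model should be fixed in writing before outcomes are compared by arm.

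The cost is wording only. Both NGAL values are needed for randomisation and baseline creatinine for the outcome, and contrast dose is already collected. The 108 per group stays as stated. The downside is small, but the covariates should be kept few: events number about 120 at the planning rates and could be about 48 if CIN is 20%.
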